## Data collection

4.

An investigator ([name], [name], or [name]) will conduct a preoperative visit with eligible participants the day before their surgery. Baseline data, recorded from participant self-report and their electronic medical records, will include age, sex, height, weight, ASA grade, complications, duration of analgesic use, admission time, and preoperative blood glucose and cortisol concentration. The NRS will be used to assess baseline pain. The Timed Up and Go test will be used to evaluate baseline knee function and active and passive knee flexion. Preoperative baseline recovery quality score will be evaluated using the QOR-15. The anesthesiologist will collect and record intraoperative data through the anesthesia management system, including dosages of sedatives and analgesics, steroid use (yes/no), blood loss, infusion volume, tourniquet use time, operation time, and any AE. An investigator ([name], [name], [name], or [name]) will collect postoperative data, including pain-related indicators, opioid consumption, knee joint function recovery indicators, and any AE. Postoperative data will be collected from the doctor and nurse management stations of the hospital information system, standardized CRF, and PCIA information storage cards (Table 1). Outcome assessors will have been trained in the standard operating procedures of clinical drug trials. The clinical data monitoring committee (DMC) will supervise all data collection to ensure reporting accuracy, integrity, readability, and timeliness. All source files will be rigorously cleaned to ensure accurate data use.

**Table 1 tab1:** Study protocol.

Outcome measure	Visit 1	Visit 2	Visit 3	Visit 4	Visit 5	Visit 6	Visit 7
Time	1 day pre- surgery	During operation	PACU	Within 12 h post-surgery	POD 1	POD 2	Hospital discharge
Eligibility screening	X	–	–	–	–	–	–
Informed consent	X	–	–	–	–	–	–
Demographic characteristics	X	–	–	–	–	–	–
Preoperative education	X	–	–	–	–	–	–
Baseline measures	X	X	–	–	–	–	–
Randomization	X	–	–	–	–	–	–
Intervention	–	X	–	–	–	–	–
Incidence of rebound pain	–	–	–	X	X	–	–
First time to begin pain cycle	–	–	–	X	X	–	–
First time rebound pain occurred	–	–	–	X	X	–	–
NRS scores	X		X	X	X	X	–
Cumulative opioid consumption	–	X	X	X	X	X	–
Timed Up and Go test	X	–	–	–	X	–	–
Range of motion of knee joints	X	–	–	–	X	–	–
Time to reach discharge standard	–	–	–	–	–	–	X
Length of stay	–	–	–	–	–	–	X
Blood glucose and cortisol concentration	X	–	–	–	X	–	–

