## Statistical methods

7.

We plan to include data from all the participants assigned to randomized grouping, regardless of intervention, in a intention-to-treat analysis. SPSS version 25.0 will be used to analyze data. The Shapiro–Wilk test will be used to assess normality of continuous variables. Normal data will be described as means ± standard deviations, and otherwise as medians and interquartile ranges. Demographic and intraoperative data will be compared by independent samples *t*-tests, Mann–Whitney U test, chi-square test, Yates’ chi-square test, or Fisher’s exact probability test, as appropriate. The primary study outcome (rebound pain) is dichotomous, and the relative risk (RR) and 95% confidence interval (CI) will be calculated using the modified Poisson regression model for the esketamine and placebo groups. We plan to evaluate three modified Poisson regression models: model 1 will be unadjusted; model 2 will be adjusted for gender, age, BMI, ASA grade, complications, long-term analgesics use, and baseline pain score; model 3 will be adjusted for tourniquet use time, operation time, steroid use (yes/no) and analgesic and sedative doses during the operation. We plan to conduct a sensitivity analysis on the primary outcome. The effects of the intention-to-treat set and the per-protocol set on the consistency of the primary outcome will be compared. The per-protocol set will be whether the participant has completed all main baseline variables, has not violated the inclusion or exclusion criteria, has completed all trials and assessments, and was in good adherence. Second, we plan to compare the impacts of different statistical methods (i.e., stratified chi-square test and modified Poisson regression model) on the consistency of the primary outcome. Stratified chi-square analysis adjusted for major potential confounders, i.e., age, sex, use of steroids (yes/no), preoperative pain score, and long-term use of analgesics (yes/no) before surgery. Adjusted OR values will be calculated using the Cochran–Mantel–Haenszel test (CMH).

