Secondary outcomes will be exploratory, without adjustment for multiple comparisons. The first time to enter the pain cycle within the first 24 postoperative hours and the first time to rebound pain within the first 24 postoperative hours will constitute the survival data. Kaplan–Meier survival curves and log-rank tests will be used to analyze survival data, and univariate COX regression will be used to calculate HR and 95% CI. NRS and opioid use at different postoperative intervals will constitute repeated-measurement data. Generalized estimation equation (GEE) will be used, with patient identification number as the main variable, time as the main internal variable, and NRS and opioid consumption as the dependent variables. Independent samples *t*-tests or Mann–Whitney U tests will be used to compare independent data between the groups. The Hodges–Lehmann method will be used to evaluate the pseudo-median differences and 95% CI. Categorical data will be expressed as the number of cases (percentage) and analyzed using the chi-square test, Yate’s chi-square test, or Fisher’s exact probability test. Safety outcomes will be analyzed using the safety analysis dataset. All participants who undergo randomization and for whom post-trial safety evaluation data are available will be included in the safety analysis dataset. All statistical tests will be two-sided and *p* < 0.05 will be considered statistically significant.

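### The two exploratory time-to-event outcomes are fixed on a treatment-only Cox model, giving up some efficiency that baseline covariates already collected could supply

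*Protocol article*

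**What the plan says.** Statistical methods (section 7) names two survival outcomes, time to the first pain cycle and time to the first rebound pain, each followed for 24 h. For both it fixes Kaplan–Meier curves with a log-rank comparison, and for the effect estimate it states that "univariate COX regression will be used to calculate HR and 95% CI". The article mentions no adjusted Cox model and no stratified log-rank test.

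For the primary outcome, incidence of rebound pain within 12 h, the same section plans three modified Poisson models. The first is unadjusted. For the second, "model 2 will be adjusted for gender, age, BMI, ASA grade, complications, long-term analgesics use, and baseline pain score". The third uses intraoperative variables. None of the three is named as the main one. A sensitivity analysis by the Cochran–Mantel–Haenszel method stratifies on what the plan regards as the major potential confounders: "age, sex, use of steroids (yes/no), preoperative pain score, and long-term use of analgesics (yes/no) before surgery".

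The covariates are in hand. Data collection (section 4) says of the preoperative visit that "The NRS will be used to assess baseline pain", and its list of baseline data includes "ASA grade, complications, duration of analgesic use, admission time, and preoperative blood glucose and cortisol concentration".

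On the standing of these outcomes, section 7 is explicit: "Secondary outcomes will be exploratory, without adjustment for multiple comparisons".

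**The concern.** Time to first rebound pain is the time to the first NRS of 7 or more (Secondary outcomes, section 3.2). It comes from the same patients and the same pain diary as the primary outcome. The plan treats baseline pain and long-term analgesic use as related to whether rebound pain occurs, yet leaves them out when it models when rebound pain occurs, and gives no reason for the difference.

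The hazard ratio is non-collapsible. When a prognostic covariate is omitted, the treatment hazard ratio is pulled toward 1 and its test loses power, even under perfect randomization. At stake is some sensitivity in the outcomes meant to show whether esketamine delays severe pain as well as making it less frequent. Validity is not at stake.

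**Working it through.** **1. The plan's own figure.** Sample size calculation (section 2.6) gives a 45% control incidence, a 35% reduction over the first 12 h, α = 0.05 and power 80%; section 7 makes the tests two-sided. Read as relative, the reduction gives 0.45 × 0.65 = 0.2925.

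- n = [1.960·√(2·0.37125·0.62875) + 0.842·√(0.45·0.55 + 0.2925·0.7075)]² / 0.1575² = 147 per group, or 159 with continuity correction. The plan states 160.
- 160 / 0.90 = 177.8, so 178 per group, as stated.
- Read as an absolute difference (45% against 10%), the result is only 25 to 30 per group, so the relative reading is the one used.

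**2. From incidence to hazard ratio.** Both incidences are 12 h figures; the document gives none at 24 h. Under constant hazards (an assumption):

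- HR = ln(1 − 0.2925) / ln(1 − 0.45) = 0.579.
- Events by 12 h with 160 per group: 160 × (0.45 + 0.2925) = 118.8. Schoenfeld: √(118.8/4) × |ln 0.579| − 1.960 = 1.02, so power is 84.6%.
- Carried on to 24 h, incidences are 1 − 0.55² = 69.75% and 1 − 0.7075² = 49.94%, or 160 × 1.1969 = 191.5 events. The simulation with no covariate effect averaged 191.

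**3. Unadjusted against adjusted Cox model.** Simulation with 320 patients (160 per arm, after withdrawal), 2,500 runs per setting, control 12 h incidence calibrated to 45% and censoring at 24 h. The adjusted model contains group, baseline pain and analgesic use. Prognostic strength is assumed: HR per SD of baseline pain / HR for analgesic use, with 30% of patients using analgesics. Each cell shows power unadjusted → adjusted at 24 h.

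| Covariates (assumed HRs) | True HR 0.579 | True HR 0.70 |
|---|---|---|
| none (1.0 / 1.0) | 96.8% → 96.6% | 71.6% → 71.6% |
| weak (1.2 / 1.2) | 96.1% → 96.4% | 70.2% → 71.4% |
| moderate (1.35 / 1.5) | 95.0% → 96.4% | 65.3% → 69.9% |
| strong (1.6 / 1.8) | 91.8% → 96.1% | 59.4% → 69.2% |
| very strong (2.0 / 2.0) | 86.3% → 95.9% | 52.1% → 68.5% |

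The Monte Carlo standard error of a single figure is √(0.95 × 0.05/2500), about 0.4 points, near 95%, and about 1.0 point near 65%. Both models are fitted to the same simulated data sets.

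**4. Type I error.** At a true HR of 1.0 the 24 h rejection rate was 4.5% to 5.6% across both models.

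**5. Where the gain comes from.** In the moderate case at HR 0.579, the estimated HR was 0.592 unadjusted and 0.577 adjusted, with standard errors of 0.148 and 0.149. In the strong case it was 0.610 and 0.576, with standard errors of 0.149 and 0.150. The gain is a hazard ratio further from 1, not a smaller standard error.

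**6. If few first events fall after 12 h.** Censoring the same runs at 12 h gave, at HR 0.579, 83.5% → 83.3% (none), 82.9% → 84.8% (moderate) and 79.6% → 84.8% (strong). The pattern does not depend on the extrapolation to 24 h.

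No incidence is stated for the first pain cycle, so the figures are calibrated to rebound pain only.

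**The case against.** The strongest reply is that nothing here is an error. A treatment-only Cox model is a legitimate pre-specified choice in a randomized trial, the outcomes are exploratory, and the t-tests, rank tests and chi-square tests planned for other secondary outcomes are unadjusted too. The univariate Cox model also matches the log-rank test closely, so curve, test and hazard ratio tell one story. All of this stands. It means that the present plan buys coherence and that the point is one of efficiency only.

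It is also fair that the adjusted hazard ratio answers a slightly different question, conditional on the covariates, and that the benefit is small at the plan's own effect size: 0.3 points with weak covariates and 1.4 with moderate ones. Larger gains need stronger covariates or a smaller treatment effect, and both are assumptions.

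A statistical analysis plan that is not shown may add an adjusted model. But the article does not leave the model open; it states one. The point concerns that stated choice.

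A reader might also infer that the univariate hazard ratio cannot be set beside the adjusted relative risk. The document does not support that. An unadjusted relative risk is planned in model 1. The windows differ, 12 h for the primary outcome and 24 h here. First pain cycle is a different event, the initial analgesic intervention. A hazard ratio and a relative risk are different measures whatever the adjustment, so adjusting would not make them alike.

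**Conclusion.** The point holds as a minor efficiency point. The plan fixes a treatment-only Cox model for both outcomes while holding, before surgery, two covariates that it treats as related to rebound pain elsewhere in the same section. The loss is nil if those covariates are not prognostic, about 0.3 to 5 points of power if they are weak to moderate, and about 4 to 10 points if they are strong, over true hazard ratios of 0.579 and 0.70. These sizes rest on assumed prognostic strength, a 30% prevalence of analgesic use, constant hazards and a correctly specified adjusted model. The document gives none of these.

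Two stronger readings should be resisted. The unadjusted analysis is not invalid: its type I error is about 5%, and its hazard ratio nearer to 1 is the marginal quantity, not an error. Nor does the plan contradict its primary analysis: adjustment appears in model 2 and the stratified sensitivity analysis, model 1 is unadjusted, and no model is named as the main one.

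**What to change.** In section 7, replace the univariate model by one Cox model per outcome with group plus pre-randomization covariates: at least baseline NRS, long-term analgesic use, age and sex. Leave out the intraoperative variables of model 3, including steroid use, because they arise after randomization. State that the main hazard ratio, 95% CI and p-value all come from this model, and that the Kaplan–Meier curves, log-rank test and univariate hazard ratio are supportive. Naming which result governs matters, because the adjusted model and the log-rank test may differ slightly.

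The cost is a sentence or two of text and no new data. The small downside is that the reported hazard ratio becomes conditional on the covariates, which the report should say.

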**Methods/design:**

This study is a single-center, prospective, double-blind, randomized, placebo-controlled trial. Participants who plan to undergo total knee arthroplasty will be randomly assigned to the esketamine group (*N* = 178) and placebo group (*N* = 178) in a ratio of 1:1. This trial aims to evaluate the impact of esketamine on postoperative rebound pain in patients undergoing total knee arthroplasty. The primary outcome of this trial is the incidence of rebound pain within 12 h after the operation in the esketamine group and the placebo group. The secondary outcome will be to compare (1) the incidence of rebound pain 24 h after the operation; (2) the time to enter the pain cycle for the first time within 24 h after the procedure; (3) the first time of rebound pain occurred within 24 h after surgery; (4) the modified rebound pain score; (5) NRS score under rest and exercise at different time points; (6) the cumulative opioid consumption at different time points; (7) patient’s prognosis and knee joint function evaluation; (8) blood glucose and cortisol concentration; (9) patient’s satisfaction score; (10) adverse reactions and adverse events.

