### Secondary outcomes

3.2.

Incidence of rebound pain within the first 24 postoperative hours.Time to entering the first pain cycle during the first 24 postoperative hours (i.e., time from PACU transfer to initial analgesic intervention).Time to first rebound pain during the first 24 postoperative hours (i.e., time from PACU transfer to first NRS ≥ 7).The modified rebound pain score (MRPS). MRPS = HNRS−LoNRS (PACU) (2), where HNRS (24) is the highest NRS pain score within 24 h after regional nerve block, and LoNRS (PACU) is the lowest NRS pain score while in the PACU.NRS scores at rest (i.e., laying quietly) and exercise (i.e., raising the affected limb ≥5 times to ≥30 cm) at: 1 day before their operation, PACU transfer, the morning of the first postoperative day; during physical therapy on the first postoperative day; the evening of the first postoperative day; the morning of the second postoperative day; and the evening of the second postoperative day. Morning is defined as 8–10 a.m. and evening as 8–10 p.m.The cumulative opioids upon transfer to the PACU and at 12, 24, and 48 postoperative hours. Cumulative opioids includes administration of basic and remedial analgesics, which will be converted to ‘morphine-equivalent dose’ for analyzes.One day before their operation and first postoperative Timed Up and Go test (i.e., time required to stand up from a standard-height armchair, walk forward three meters, walk back to the chair, and sit down).Range of motion [i.e., degree of the affected knee joint from neutral (0°) to maximum flexion] of the active and passive knee joints at 1 day before their operation and on the first postoperative day.Time to discharge (i.e., when the participant can walk from bed to bathroom independently and along the corridor without the help of a walker).Length of stay (i.e., number of days from admission to discharge).Quality of Recover (QOR)-15 scores at 1 day before their operation and the first postoperative day.Blood glucose and cortisol concentration at admission and the first postoperative day.Patient satisfaction at discharge, where 1 point is ‘unsatisfactory’, 2 points is ‘relatively satisfactory’, and 3 points is ‘satisfactory’.

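### The GEE for NRS and opioid use lists its variables without treatment group, group-by-time or the preoperative NRS, so as listed it does not yield the promised esketamine–placebo contrast

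*Protocol article*

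**What the plan says.** Section 7 of the protocol article states that "NRS and opioid use at different postoperative intervals will constitute repeated-measurement data". It assigns both outcomes to a GEE and gives the variables "with patient identification number as the main variable, time as the main internal variable, and NRS and opioid consumption as the dependent variables". Soon after comes "Independent samples *t*-tests or Mann–Whitney U tests will be used to compare independent data between the groups", followed by Hodges–Lehmann differences with 95% CI.

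The abstract (Methods/design) introduces the list of secondary aims with "The secondary outcome will be to compare (1) the incidence of rebound pain 24 h after the operation"; item (5) of that list is NRS at rest and exercise and item (6) is cumulative opioid consumption.

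Section 3.2 (Secondary outcomes) schedules NRS at rest and exercise once before surgery and at six times afterwards. It defines the opioid outcome as "The cumulative opioids upon transfer to the PACU and at 12, 24, and 48 postoperative hours". Section 4 (Data collection) and Table 1 confirm that a baseline NRS is taken at the preoperative visit.

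On status, Section 7 says "Secondary outcomes will be exploratory, without adjustment for multiple comparisons", and also "All statistical tests will be two-sided and *p* < 0.05 will be considered statistically significant".

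**The concern.** A GEE needs three things stated: how observations are clustered and ordered, what the outcome is, and which effects are estimated. Section 7 gives the first two and leaves out the third. The effect that matters in a randomised trial, the difference between arms and how it varies over time, is not in the list.

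This leaves open, for two outcomes measured repeatedly, which quantity will be reported: a group effect averaged over all times, an interaction test, or differences at single times. These can give different answers. Because secondary tests are unadjusted at the 0.05 level, leaving the choice until the data are seen invites selection.

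Two features of the outcomes make the choice more than a formality. The opioid outcome is a running total, which cannot fall, so a time effect on it says nothing about treatment. And the preoperative NRS is collected in the same rest and exercise form as the outcome but has no stated role in this model, although Section 7 does adjust the primary analysis for baseline pain in its second model.

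**Working it through.** The plan gives no figure for this analysis, so there is nothing to reproduce. The sample size in Section 2.6 concerns the primary outcome and has no bearing here. The check is a reading of the text with two pieces of simple arithmetic.

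**1. Terms listed against terms needed**

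| Role in the model | Stated in Section 7? |
|---|---|
| Subject (cluster) | Yes: patient identifier |
| Within-subject index | Yes: time |
| Outcome | Yes: NRS; opioid consumption |
| Treatment group | No |
| Group-by-time | No |
| Preoperative NRS as covariate | No |

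No other section adds the missing terms. By comparison, the relative risk for the primary outcome is "calculated using the modified Poisson regression model for the esketamine and placebo groups", so the section does name the arms where it describes its main model.

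**2. Does another stated method fill the gap?**

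The sentence on t-tests and Mann–Whitney tests does compare the groups, but for independent data. NRS and opioid use have just been classed as repeated measurements. The natural reading is that they belong to the GEE and not to this sentence, though the text does not strictly rule out a test at a single time.

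**3. What an averaged group effect would mean for cumulative opioids**

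Input: the four times in Section 3.2. Let d0 be the dose up to PACU transfer, d1 the dose from then to 12 h, d2 from 12 to 24 h, and d3 from 24 to 48 h. The four recorded totals are:

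- PACU transfer: d0
- 12 h: d0 + d1
- 24 h: d0 + d1 + d2
- 48 h: d0 + d1 + d2 + d3

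Their sum is 4·d0 + 3·d1 + 2·d2 + d3, and their mean is d0 + 0.75·d1 + 0.5·d2 + 0.25·d3. A group main effect that weights the four times equally would therefore count the earliest use four times and the 24–48 h use once. The plan does not propose such an analysis. The calculation shows only that adding a bare group term would not be an adequate repair for this outcome.

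**4. What the preoperative NRS could add**

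For the difference between arms at one time, adjusting for a baseline with correlation r to the outcome multiplies the variance by about 1 − r². The documents give no r, so a range of 0.2 to 0.4 is assumed.

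- r = 0.2: 1 − 0.04 = 0.96, a 4% reduction in variance; the confidence interval narrows by a factor √0.96 ≈ 0.98
- r = 0.4: 1 − 0.16 = 0.84, a 16% reduction; the factor is √0.84 ≈ 0.92

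This is a modest gain in precision. A randomised comparison without the covariate would still be valid.

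**The case against.** The strongest reply is that nobody would run this GEE without a group term. The trial has two arms and the abstract says the secondary outcomes are to be compared. The surrounding sentences on log-rank, Cox and chi-square tests do not name the group either, yet they are plainly between-arm analyses. A journal article may also leave the fixed effects, covariates and contrasts of exploratory models to a full protocol or SAP that is not shown.

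Most of this stands. A group comparison was very probably intended, and the outcomes are exploratory. What does not follow is that the sentence needs no correction. The article does not merely name the method and defer the rest. It sets out the variables of the model and leaves out the one that carries the randomised comparison. For a log-rank test, naming the method largely fixes the comparison; for a longitudinal model it does not, because a main effect, an interaction and time-specific differences are all possible.

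It is also fair to say that the baseline covariate is an improvement and not the repair of an error, and that the nested-totals argument concerns an analysis the plan does not contain. Both belong in the recommendation, not in the charge.

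**Conclusion.** The GEE as listed in Section 7 does not yield the esketamine–placebo contrast for NRS and cumulative opioids, secondary outcomes (5) and (6) of the abstract. This is a specification defect in exploratory analyses; the primary outcome, its model and the sample size are unaffected. It should be corrected, but it does not threaten the trial's main conclusion.

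Two stronger readings should be resisted. A reader might infer that the sentence prescribes a time-only model, testing whether pain and opioid totals change over time. It does not: the items listed are subject, within-subject and outcome roles, and time as a within-subject index is not by itself a stated effect. The list of predictors is incomplete; it does not specify a different test. A reader might also infer that the arms will never be compared on these outcomes. The stated aim points the other way, and the between-group tests named in the same paragraph could be applied at a single time.

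The 4–16% reduction in variance rests on the assumed correlation of 0.2–0.4. The statements about the listed terms and the nested totals need no assumption beyond the text.

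**What to change.** Restate the model in Section 7, before unblinding:

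- **Terms.** Treatment group, time as a categorical factor, and group-by-time, with patient as the cluster.
- **NRS.** Separate models at rest and on exercise, each with the matching preoperative NRS as a covariate. The reported result is the between-group difference with 95% CI at each of the six postoperative times.
- **Opioids.** The between-group difference in cumulative dose, with 95% CI, at each stated time; or a model of the dose used in each interval. Do not report a time effect, or a group effect averaged over the nested totals, as the finding.

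This gives 2 × 6 = 12 NRS differences and, if cumulative doses are used, 4 opioid differences. As they are exploratory and unadjusted, they are best read as estimates with intervals.

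The cost is about two sentences. No new data are needed, since the preoperative NRS is already collected, and the same software procedure serves.

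### QoR-15, Timed Up and Go, range of motion, glucose and cortisol have preoperative values that the planned unadjusted comparisons do not use: a modest, avoidable loss of precision on exploratory outcomes

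*Protocol article*

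**What the plan says.** **Measurement.** Secondary outcomes (section 3.2) schedules each outcome once before surgery and once after:

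- QoR-15: "scores at 1 day before their operation and the first postoperative day".
- Timed Up and Go: "One day before their operation and first postoperative Timed Up and Go test". Table 1 places the second test on POD 1.
- Range of motion: "active and passive knee joints at 1 day before their operation and on the first postoperative day".
- Glucose and cortisol: "Blood glucose and cortisol concentration at admission and the first postoperative day".

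Data collection (section 4) treats the first values as baseline data: "Preoperative baseline recovery quality score will be evaluated using the QOR-15", and the list of baseline variables includes "preoperative blood glucose and cortisol concentration". Table 1 shows the same two time points for all of these except QoR-15, which has no row there.

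**Analysis.** Statistical methods (section 7) sends the two time-to-event outcomes to Kaplan–Meier, log-rank and univariate Cox methods, and postoperative NRS and opioid use to generalised estimating equations (GEE). For the rest it says that t-tests or "Mann–Whitney U tests will be used to compare independent data between the groups", and that "The Hodges–Lehmann method will be used to evaluate the pseudo-median differences and 95% CI". No baseline covariate, ANCOVA or change score is named for any secondary outcome. Covariate adjustment is described for the primary outcome only, where baseline pain enters both Model 2 and the stratified chi-square (Cochran–Mantel–Haenszel) sensitivity analysis. The same section labels the secondary outcomes exploratory.

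**The concern.** A two-sample t-test, a Mann–Whitney test and a Hodges–Lehmann shift estimate all compare postoperative values without regard to where each patient started. When the preoperative value predicts the postoperative one, part of the spread within each arm is explainable, and these methods leave it in the error term. The intervals for functional recovery and stress markers are then wider than the collected data require. The plan already adjusts for baseline pain on the primary outcome, so using an outcome's own baseline would fit its approach.

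**Working it through.** **1. The plan's own figure.** No sample size is stated for these outcomes. The only one is for the primary outcome (section 2.6): 45% in the placebo arm, 35% lower under esketamine, α = 0.05 (two-sided per section 7), power 80%. Read as a relative reduction, 0.45 × 0.65 = 0.2925. The two-proportion formula gives 147 per group without and 159 with a continuity correction, against the stated 160. Withdrawal: 160 / 0.9 = 177.8, so 178 per group and 356 in all. The stated numbers reproduce, and 160 per arm is used below as the evaluable size.

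**2. Which analysis applies.** The outcomes in question are continuous, have one postoperative value each, and are neither time-to-event nor among the two named for GEE. That leaves the t-test or Mann–Whitney sentence.

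**3. Formulas.** Let r be the within-arm correlation between the preoperative and first-day values, with equal SDs of 1 at both times. The documents do not give r, so it is assumed over a range.

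- Unadjusted comparison: residual variance 1.
- ANCOVA: residual variance 1 − r², interval width ratio √(1 − r²), equivalent unadjusted size 160 / (1 − r²).
- Change score: variance 2(1 − r).

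The unadjusted comparison has 80% power for a standardised difference of (1.960 + 0.842) × √(2/160) = 0.313. Power of the other analyses at that same difference is Φ(2.802 / √variance − 1.960).

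| r | ANCOVA variance | Interval width ratio | 160 per arm acts like | Power, unadjusted | Power, ANCOVA | Power, change score |
|---|---|---|---|---|---|---|
| 0 | 1.00 | 1.00 | 160 | 80% | 80% | 51% |
| 0.2 | 0.96 | 0.98 | 167 | 80% | 81.6% | 60% |
| 0.3 | 0.91 | 0.95 | 176 | 80% | 83.6% | 66% |
| 0.5 | 0.75 | 0.87 | 213 | 80% | 89.9% | 80% |
| 0.7 | 0.51 | 0.71 | 314 | 80% | 97.5% | 95% |

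The width ratio does not depend on the 160. At r = 0 the price of ANCOVA is one degree of freedom.

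**4. Simulation check.** With 3,000 normal-data trials per setting, power for t-test / Mann–Whitney / ANCOVA was 79 / 78 / 82% at r = 0.3, 80 / 78 / 90% at r = 0.5 and 79 / 77 / 97% at r = 0.7. This agrees with the formulas.

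**5. Chance imbalance.** The SD of a chance standardised baseline difference is √(2/160) = 0.11. It carries into the outcome difference in proportion to r: at r = 0.5, one such SD moves the estimate by 0.5 × 0.11, about 0.06 SD. The unadjusted standard error already allows for this.

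**The case against.** **The assignment is inferred.** The t-test and Mann–Whitney sentence names none of these outcomes and does not say whether the first-day value or the change is compared. A journal article may also leave covariates for exploratory outcomes to a fuller plan. The inference does stand as one by elimination. The article is not silent: it names a test and an estimator for the remaining continuous data and describes adjustment only elsewhere. If change scores were meant, ANCOVA would still be no worse, since 2(1 − r) − (1 − r²) = (1 − r)² ≥ 0.

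**The gain is unknown and may be small.** This stands. First-day values follow surgery, two regional blocks and opioid analgesia, so a modest correlation with preoperative function is plausible. At r = 0.3 the interval narrows by only about 5%, and nothing in the documents supports r = 0.7 in particular.

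**Stronger readings that the documents do not support:**

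- A reader might infer that the comparisons are biased or invalid. Under 1:1 randomisation they are neither.
- A reader might infer that the GEE deliberately leaves out baseline NRS. That sentence lists only patient, time and the dependent variables. It omits even treatment group, so it is abbreviated and cannot show what was excluded.
- A reader might infer that baseline values serve only description apart from Model 2. Preoperative pain is also used in the Cochran–Mantel–Haenszel analysis.

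**Conclusion.** The point holds as a minor matter of efficiency. As written, the plan compares outcomes that have their own preoperative measurement by methods that make no use of it. For an assumed correlation of 0.3 to 0.7, the intervals are wider than an ANCOVA on the same patients would give, the latter being narrower by about 5% to 29%. Below about 0.3 the difference is slight.

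This rests on three things: the assignment of these outcomes to the unadjusted tests by elimination, the assumed range of r, and a roughly linear relation with similar variance before and after surgery. No sample-size figure and no primary conclusion changes.

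**What to change.** In section 7, state that the first-postoperative-day values of QoR-15, Timed Up and Go, active range of motion, passive range of motion, glucose and cortisol will each be analysed by ANCOVA with group and that outcome's own preoperative value as terms. Report the adjusted mean difference and 95% CI with robust standard errors. Fix the robust standard errors now, so that no choice of scale or method depends on the unblinded data. Keep the Mann–Whitney and Hodges–Lehmann results as supporting analyses.

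Do not substitute a t-test on change scores: below r = 0.5 it has less power than the unadjusted test (66% against 80% at r = 0.3).

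As a minor addition, name the preoperative NRS as a covariate in the NRS GEE, using the rest score for the rest analysis and the exercise score for the exercise analysis. Baseline pain is already adjusted for in Model 2 and the Cochran–Mantel–Haenszel analysis. Adding a QoR-15 row to Table 1 would make the schedule match section 3.2.

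The cost is a few sentences of wording. No new data, visits or patients are needed.
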